### Study procedure

#### Recruitment

All patients that sustained an (initial or recurrent) ankle sprain and of whom a mortise view and lateral radiograph is made, will be identified per ER of each participating hospital. These patients will be screened according to the in- and exclusion criteria (Table 1). All patients eligible for inclusion were approached for verbal informed consent. Patients are selected based on presentation at the ER. As these patients, out of the many patients who sustain an initial ankle sprain, experience severe enough complaints to actively reach out for help, these sprains may be regarded as ‘severe’ and therefore these patients may be more prone to persistent complaints. Also these patients can be monitored in case of a high risk of CAI in case of an initial sprain, as they have already been identified by the medical healthcare system, and radiographs have been made (according to standard protocol avoiding extra medical costs) which may be used to identify the size of the risk at CAI. All patients that were included and already suffered from recurrent ankle sprains, or CAI even, received the same follow-up as the patients who suffered from an initial sprain and were included in the sub-group analysis.

#### Follow-up

A legally required waiting period of two weeks is observed prior to asking consent and sending the questionnaires to the patient’s home address or email address. Patients are asked to fill out the first questionnaire immediately which gives a T0 (baseline measure at approximately two weeks after the initial sprain). The subsequent evaluation time points are T1 interim evaluation after three months, T2 after six months, and T3 at twelve months. The questionnaires contain questions about patient characteristics, previous ankle sprains, treatment, restrictions and complaints. Additionally the questionnaires contains the Foot and Ankle Outcome Score (FAOS) and the Cumberland Ankle Instability Tool (CAIT) to evaluate recovery. To ensure all patients with CAI are identified, one year after their ER visit they will be contacted, inquiring on persisting complaints and ankle instability. Patients that indicate on the first questionnaire they sustained ankle sprains prior to their ER visit will not receive further follow-up questionnaires, as these patients are considered to have CAI and therefore need no extra monitoring to identify whether they develop CAI or not. They will not be included in the primary analysis as this may lead to overfitting of the current model. Concomitant neuromuscular adaptations and additionally may follow a different rehabilitation route due to familiarity with the complaints.

In case of persisting complaints six months after the ER visit, patients will be eligible for surgical treatment according to Dutch standards. This is to avoid unnecessary invasive treatment on patients as a large proportion recover by means of conservative treatment [7].

### Clinical outcome measures

The first outcome measure is the radiograph made at the ER. This radiograph will be assessed for nine bone geometric characteristics. These characteristics will be implemented in the model in case they show a correlation with developing CAI: ankle alignment using the medial distal tibial angle (MDTA) measured as (1) the absolute angle and whether this angle was considered a (2) varus (<87^o^), normal (87-91^o^) or valgus (>91^o^) position [27], fibular position in relation to the tibia measured as (3) projected distance and (4) relative distance [28], and tibiotalar contact ratio assessing the (5) talar height, (6) radius and (7) angle between the talus and tibia, (8) the angle representing the height of the medial malleolus and (9) the talar curvature (Figs. 2, 3 and 4) [29]. Additionally (10) the Medial Malleolar Height Angle (MMHA) and (11) the Talar Convexity Angle (TCA) [30] (Figs. 5 and 6).

**Fig. 2 Fig2:**
[figure not shown]
Alignment assessment using the medial distal tibial angle (**b**). This angle (arrows) is formed by the tibial axis (**a**-**b**) and the joint orientation line of the distal tibia (**c**). The MDTA was measured in two ways: (1) the absolute angle and whether this angle included a (2) varus (<87^o^), normal (87-91^o^) or valgus (>91^o^)

**Fig. 3 Fig3:**
[figure not shown]
The fibular position is assessed drawing two lines from the edge of the anterior tibia to the posterior part of the tibia (**b**) cq. the anterior part of the fibula (**a**). The absolute distance is measured using the projected posterior distance in millimeters (mm) of the fibula in relation to the tibia (height a in mm); and the relative fibular position is assessed as a posterior position in terms of percentage (a divided by b in %)

**Fig. 4 Fig4:**
[figure not shown]
The tibiotalar contact ratio is assessed using 3 variables: the talar radius (**r**); the talar height (**h**); and the tibiotalar sector (**α**). By drawing a circle digitally fitted to the talar joint surface, the radius is determined by drawing a line to the middle of the circle, measured in millimeters (**r**). The height is determined drawing a line through the middle of the circle from the surface of the talus to the inferior border, measured in millimeters (**h**). From the center of the circle two lines are drawn to the anterior and posterior margins of the distal tibia, representing the tibiotalar sector (**α**)

**Fig. 5 Fig5:**
[figure not shown]
Medial Malleolar Height Angle (MMHA) formed by the angle connecting the distal tibial joint line (**a**-**b**) and the line from the most lateral point of the tibiotalar joint line to the most distal point of the medial malleolus (**b**-**c**)

**Fig. 6 Fig6:**
[figure not shown]
The Talar Convexity Angle (TCA) is formed by connecting the posterior talar tubercle (**a**), the most proximal part of the talus (**b**), and the deepest point of the transition to the talar neck (**c**)

Secondly, (12) age, (13) sex, (14) height, (15) BMI and (16) sports intensity (by means of the Ankle Activity Index (AAI)) will be implemented in the model as important patient characteristics, in case of a significant correlation. All these variables have shown a (prospective or retrospective) correlation with ankle instability in previous research apart from MDTA, MMHA and TCA. These three, however, have shown a relation with other pathologies that also concern an inversion-plantarflexion trauma mechanism and will therefore be explored on a potential correlation with CAI [14, 16, 30].

To assess overall recovery and CAI at 12 months, a questionnaire including patient reported outcome measures (PROMs) will be used. This questionnaire includes the FAOS and CAIT. The FAOS is a Dutch validated questionnaire assessing pain, other symptoms (swelling, locking, mobility, stiffness), function (activities of daily living) and sports and foot- and ankle related quality of life divided over 5 subscales, with scores ranging from 0 to 100 [31, 32]. The CAIT is scale consisting of 9-items measuring the severity of functional ankle instability per ankle individually. The total score ranges from 0 to 30 with a cut-off value discriminating between a functionally stable and instable ankle of 11.5 points (as calculated for the Dutch population) [33, 34].

### Analyses

#### Inter- and intra-observer reliability

Two radiology residents, an orthopedic resident and an emergency physician of the AMC will be included in the inter- and intra-observer reliability assessment. These professionals are selected because the orthopedic surgeon eventually treats the patient with CAI, and the emergency physician is the first to see a patient at the ER after a severe ankle sprain and the radiologists assess the radiographs. Radiologists are most experienced in radiographic assessment and are therefore be considered as reference standard, i.e. to assess inter-observer reliability the measurements by the orthopedic resident and emergency physician are compared to the measurements performed by the radiology residents. To assess intra-observer reliability 39 radiographs are assessed twice by each observer with a minimum of 2 weeks in between. In order to prepare the reliability assessment a calibration session will be held with all observers. If this proves the measurements can be performed reliably they will be implemented in the other participating hospitals after a calibration meeting and practice session.

#### Prognostic value of variables

To determine whether the variables, selected from current literature, can be implemented in our model, it has to be determined whether they are of prognostic value on the progression of an ankle sprain to CAI. This will be done by determining whether they have an individual correlation with instability 12 months after an ankle sprain and whether this correlation is influenced using a multivariate analysis. In case of no existing correlation, factors are left out of the model and the sample size is recalculated accordingly.

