#### Assessment of agreement

Assessment of the prognostic value of the fourteen variables will be performed on the sample size of the internal validation [36]. To avoid overfitting, the prognostic value of these 16 variables will be assessed when 10 events per variable (EPV) is reached [37]. With a maximum of sixteen variables with a minimum of 10 events per variable, a prevalence of 30–40% after an initial sprain, including a 10% loss-to-follow-up, a sample size of 593 patients is needed to assess their prognostic value (Table 2).

**Table 2 Tab2:** Sample Size calculation prognostic value, internal validation [38, 39]

EPV = no. of events/no. of regression coefficients		
Minimal EPV	≥10 Prognostic Value	≥20 Prediction Model
Change of developing CAI	30–40%	30–40%
No. of regression coefficients	16	16
(? = no of events needed)	10 =?/16 ? = 160 minimal 160 events	20 =?/16 ? = 320 → minimal 320 events
In case of 30% chance of developing CAI	160*3.33 = 532.8 patients	320*3.33 = 1065.6 patients
In case of 40% chance of developing CAI	160*2.5 = 400 patients	320*2.5 = 800 patients
Sample Size (incl. 10% loss to follow-up)	445–593 patients	889–1185 patients

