#### PREDICT sample size

For a prognostic model at least 20 EPV is needed to optimize reliability and to avoid bias in regression coefficients [37–39]. Based on having maximally 16 variables with a minimum of 20 events per variable, a prevalence of 30–40% after an initial sprain, including a 10% loss-to-follow-up, a sample size of 1185 patients is needed to perform the internal and 1185 patients is needed to perform the external model validation, resulting in a total of 2370 patients (Table 2).

During the study the required sample size may change and will be recalculated accordingly in case one of the following scenarios occur:In case one or more radiographic factors have a low inter- or intra-observer reliability (ICC ≤0.70), they will be excluded from the risk assessment model and the sample size will be recalculated using the new number of prognostic factors. If radiographic assessments cannot be performed in more than 2 cases (> 5%) a candidate predictor will be excluded, as the problem is likely to recur and therefore cannot be adequately assessed, now and during future assessment (e.g. up to 5% missing data is accepted) [40, 41].In case of multicollinearity between (ICC > 0.70) between prognostic variables one will be excluded;If a variable lacks agreement (ICC ≤0.70) with CAI it will be excluded;In case the prevalence of CAI during the study differs from the estimated 30%. In case the percentage of patients progressing to CAI exceeds the 50%, the sample size calculation will be based on the number of non-events. The prevalence will be recalculated when 500, 750, 1000, 1250, 1500, 1750,2000 and 2250 patients have returned the last questionnaire to minimize patient burden, as inclusion will stop as soon as the minimal required sample size is reached.

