#### Prognostic value of variables

Depending on normality of data the Pearson or Spearman correlation coefficients will be used to assess correlations. A scatterplot for numerical data and Odds Ratio (OR) for binary data will be used to provide additional information on possible correlations in the data between prognostic factors. In case of correlations (*p* < 0.10 to avoid overfitting [40]) shown by an univariate analysis, a multivariate logistic regression will be performed to assess dependency between variables. The R^2^ will be used to visualize model fitness for the contribution of a factor to the progression to CAI and for the full model.

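### The sample size may be lowered when predictors are dropped for lack of association with CAI, so 20 events per variable is counted on the survivors and not on all candidates tested

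*Protocol article*

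**What the plan says.** Sample size calculation, Table 2, defines "EPV = no. of events/no. of regression coefficients" and uses 16 coefficients. Two stages follow. In Assessment of agreement, "the prognostic value of these 16 variables will be assessed when 10 events per variable (EPV) is reached", and this is done on the internal validation (development) sample. In PREDICT sample size, "For a prognostic model at least 20 EPV is needed to optimize reliability and to avoid bias in regression coefficients", and the resulting 1185 patients are required once for internal and once for external validation, 2370 in total.

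The recalculation rule appears twice. Analyses, Prognostic value of variables: "In case of no existing correlation, factors are left out of the model and the sample size is recalculated accordingly". PREDICT sample size lists several triggers for recalculation. The first, low observer reliability, states the method: "the sample size will be recalculated using the new number of prognostic factors". Another trigger looks at the outcome: "If a variable lacks agreement (ICC ≤0.70) with CAI it will be excluded". The same section adds that "inclusion will stop as soon as the minimal required sample size is reached".

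Under Data analysis and statistics, candidates are screened one at a time at p<0.10, a threshold described as a guard against overfitting. For correlations "shown by an univariate analysis, a multivariate logistic regression will be performed to assess dependency between variables". The Prognostic model section there sets the full sample size, and with it the date of the temporal split, only after this screening.

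**The concern.** Discarding a candidate because it shows no association with CAI uses the outcome data. The optimism from that search depends on the number of candidates tried, so removing the losers from the EPV denominator afterwards does not restore the protection. The article's starting calculation respects this, because it counts all 16. The recalculation rule departs from it and is tied to the point at which recruitment stops.

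The external set is affected for a different reason. No coefficients are estimated there, so the predictor count says nothing about the size it needs. The article nevertheless derives both sets from the same calculation and gives no separate minimum for the external one. The better the screen is at removing candidates, the less precise the validation becomes.

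This matters because the model is meant to yield cut-offs that advise surgery, watchful waiting or no surgery. Overfitted predicted risks are too extreme. Recruitment that has ended early cannot be repaired in the analysis.

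**Working it through.** **Inputs from the article:** 16 candidates, 10 EPV for screening, 20 EPV for the model, CAI in 30% (the lower end of 30–40%, giving the larger N), 10% loss to follow-up.

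**Reproducing the stated figures.** Events = EPV × 16; patients = events / 0.30 / 0.90.
- Screening: 10 × 16 = 160 events; 160 / 0.30 = 533.3; / 0.90 = 592.6, so 593 (stated 593).
- Model: 20 × 16 = 320 events; 320 / 0.30 = 1066.7; / 0.90 = 1185.2, so 1186 (stated 1185). Two sets: 2372 (stated 2370).

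The arithmetic is sound. The fault lies in the recalculation rule.

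**Applying the rule with k survivors.** Events = 20 × k. The last two columns give 95% half-widths in an external set of that size, assuming an AUC of 0.70 (Hanley–McNeil standard error) and a sensitivity of 0.80 (1.96 × √(0.8 × 0.2 / events)).

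| k | Events needed per set | Patients per set | Needed events ÷ 16 candidates | AUC half-width | Sensitivity half-width |
|---|---|---|---|---|---|
| 16 | 320 | 1186 | 20 | ±0.036 | ±0.044 |
| 12 | 240 | 889 | 15 | ±0.041 | ±0.051 |
| 8 | 160 | 593 | 10 | ±0.051 | ±0.062 |
| 4 | 80 | 297 | 5 | ±0.072 | ±0.088 |

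**Development set.** 20 × 8 = 160 = 10 × 16. With 8 survivors the recalculated requirement equals the screening sample, so no further development data are called for. With fewer than 8 it is smaller than what is already in hand; development then stays at 160 events, 10 per candidate tested. The equality is in events, so it holds at any prevalence.

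**External set.** No such floor exists. With 4 survivors, development remains at 593 and the external set falls to 297 patients with 80 events.

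**Illustrative simulation** (assumed: 16 independent normal predictors, 30% events, screening at p<0.10, 200 replicates). Stopping at the screening sample (533–534 evaluable) is compared with screening and fitting on the full 1067 evaluable:
- 5 real predictors at odds ratio 1.25 per SD, 11 null: calibration slope about 0.69 against 0.85; apparent versus true AUC 0.650 versus 0.604, against 0.645 versus 0.623.
- 4 real predictors at log odds ratio 0.3 per SD, 12 null: slope 0.77 against 0.89; AUC optimism 0.035 against 0.016.
- 6 weak predictors at log odds ratio 0.15, 10 null: slope 0.51 against 0.61; optimism 0.055 against 0.042.

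The direction is the same each time; the size depends on the assumed effects.

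**The case against.** **The number of survivors is unknown.** Clinical outcome measures says that most candidates have shown a correlation with instability in earlier research, so scenarios with 10 to 12 null predictors may be pessimistic. With 13 real predictors at odds ratio 1.25, about 9.3 survive, which needs about 186 events, and inclusion would continue past screening. At odds ratio 1.15 about 5.3 survive. This stands: the effect is a range, and N can also rise if CAI is rarer than 30%.

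**There are safeguards.** A bootstrap of 1000 samples is planned, but its stated purpose is bias in the regression coefficients, and it does not restore the lost events. The temporal validation set is independent of the selection, so its estimates remain unbiased; what it loses is precision. The Prognostic model section also speaks of using a full sample of 1026 for internal validation. That sits awkwardly with a stop at 593, but it is not stated as a minimum. It also does not follow from 16 predictors, and the same section sets the full size after screening.

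**Stronger readings that the article does not support.** A reader might infer that the model will be overfitted and the validation too small to show it. That is not certain: 12 survivors would leave 240 events per set. A reader might also infer that univariable screening itself promotes overfitting. That depends on the scenario. At 533 evaluable patients with 5 real predictors at odds ratio 1.25, screening gave a slope of 0.68 against 0.59 for an unpenalised fit of all 16; with 13 weaker predictors the order reversed (0.54 against 0.62). Finally, 1 − 0.9^16 = 81% might be read as the chance of keeping at least one pure-noise predictor if all were null. That needs 16 independent candidates and retention at p<0.10. Sixteen is a maximum, several measures overlap, and p<0.10 only admits a variable to the multivariable step.

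**Conclusion.** The point holds in a bounded form. As written, the rule lets N fall because of exclusions made by looking at CAI, so the claimed 20 EPV is nominal whenever candidates drop out that way. With 8 or fewer survivors, the rule requires no more development data than the screening sample, 10 events per candidate tested, and it cannot go lower. The external set has no lower limit: 240, 160 and 80 events for 12, 8 and 4 survivors, with the AUC half-width doubling from ±0.036 to ±0.072 at the last.

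This rests on reading Table 2 and the two recalculation statements together, on the article's single calculation for both sets, and on 16 candidates. The half-widths assume an AUC of 0.70, and the simulated slopes rest on assumed effects. It should be fixed before the recalculation is applied.

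**What to change.** In Analyses, Prognostic value of variables, and in PREDICT sample size, state that a factor without association with CAI may be left out of the model but does not lower the required number of events. Count EPV on all candidate coefficients examined against CAI, and keep 320 events in the development set and 320 in the external set, however many predictors survive.

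Allow a reduction only for exclusions made without looking at CAI: low observer reliability, more than 5% unmeasurable, or collinearity where the choice of variable does not use its correlation with CAI. The Discussion chooses between BMI and height by their correlation with CAI, so that exclusion should not lower N.

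Remove the statement that the p<0.10 univariable threshold avoids overfitting. Penalised estimation is an option; the counting rule is the essential change.

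Cost: wording, plus loss of the possible early stop. If 8 predictors survived, that stop would have saved 2370 − 1186 = 1184 patients, which bears on the article's aim of limiting patient burden. At 30% prevalence nothing beyond the stated 2370 is needed.

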#### Prognostic model

The main objective of this study is to assemble the required data and subsequently construct a risk assessment model for the development of CAI after a first initial ankle sprain based on patient characteristics and the ankle joint geometric characteristics. This model is based on fourteen factors that are assessed using a mortise view and lateral radiographs and a questionnaire. The patient characteristics that are implemented in the model are age, sex, height, BMI and sports intensity. Even though BMI and sports intensity may be considered as modifiable, BMI reflects the current situation and sports intensity is the level a patient wishes to return to, additionally reflecting the risk at ankle sprain exposure. Additionally nine bone geometric characteristics are implemented in the model (See clinical outcome measures).

#### Additional analyses

By comparing PROM scores over time, overall recovery will be assessed. In addition, the different treatments and symptoms during physical examination will be assessed for their relation to the functional outcome, as measured by the FAOS and CAIT and persisting complaints of instability. The final sub-analysis differentiates between the amount of recurrent ankle sprains prior to the initial ER visit to check whether the model is also applicable on patients that already suffer from CAI, as identified by the first questionnaire.

### Sample size calculation

#### Reliability assessment

For the inter- and intra-observer reliability with an expected agreement of 80% with a relative error of 20%, a sample size of 39 patients is calculated. This sample of 39 will be a subsample from the cohort of the risk assessment model [35].

#### Assessment of agreement

Assessment of the prognostic value of the fourteen variables will be performed on the sample size of the internal validation [36]. To avoid overfitting, the prognostic value of these 16 variables will be assessed when 10 events per variable (EPV) is reached [37]. With a maximum of sixteen variables with a minimum of 10 events per variable, a prevalence of 30–40% after an initial sprain, including a 10% loss-to-follow-up, a sample size of 593 patients is needed to assess their prognostic value (Table 2).

**Table 2 Tab2:** Sample Size calculation prognostic value, internal validation [38, 39]

EPV = no. of events/no. of regression coefficients		
Minimal EPV	≥10 Prognostic Value	≥20 Prediction Model
Change of developing CAI	30–40%	30–40%
No. of regression coefficients	16	16
(? = no of events needed)	10 =?/16 ? = 160 minimal 160 events	20 =?/16 ? = 320 → minimal 320 events
In case of 30% chance of developing CAI	160*3.33 = 532.8 patients	320*3.33 = 1065.6 patients
In case of 40% chance of developing CAI	160*2.5 = 400 patients	320*2.5 = 800 patients
Sample Size (incl. 10% loss to follow-up)	445–593 patients	889–1185 patients

